## Abstract

**Background:**

Participating in an adequate amount of physical activity to acquire health benefits is challenging for people with spinal cord injury (SCI) due to personal and logistic barriers. Barriers in the built and social environments may include lack of transportation, lack of accessible facilities or programs, and lack of training among fitness personnel. Low self-efficacy, lack of self-regulation skills, and improper outcome expectations are examples of personal barriers. Current approaches to investigating physical activity programs in people with SCI have been limited to traditional “one-size-fits-all” design, which has yielded low adherence rates, high dropout rates, and participants not maintaining physical activity levels at follow-up.

**Objective:**

The primary aim of this study is to test the feasibility of a tele-exercise program that applies an adaptive intervention design for 30 adults with SCI, targeting increases in adherence to the exercise program and physical activity participation.

**Methods:**

The Sequential Multiple Assignment Randomized Trial for Home-based Exercise and Lifestyle Tele-Health (SMART-HEALTH) is a 12-week, home-based, movement-to-music (M2M) program. The goal of a SMART-designed study is to develop an adaptive intervention that modifies support provisions based on response levels. In SMART-HEALTH, 2 groups of participants will undergo 3-week and 6-week asynchronous M2M interventions in the first phase. Participants who did not achieve the desired adherence rate (≥95% of video watch minutes) will be rerandomized into M2M Live (switch) or individualized behavioral coaching (augmented with the asynchronous M2M program). The study will primarily assess rates of recruitment or enrollment, adherence and retention, timing to identify nonresponders, and scientific outcomes (eg, physical activity and exercise self-efficacy). The study will qualitatively evaluate the acceptability of the study using semistructured interviews among participants who complete the 12-week intervention.

**Results:**

Recruitment procedures started in June 2022. All data are expected to be collected by September 2023. Full trial results are expected to be published by March 2024. Secondary analyses of data will be subsequently published. Results will include exercise adherence rates; changes in self-reported physical activity levels and blood pressure; and changes in secondary conditions including pain, sleep, and fatigue. Thematic analysis of semistructured interviews will include results on participant enjoyment and acceptability of SMART-HEALTH and inform modifications for future delivery of the program.

**Conclusions:**

This study will strengthen our understanding of the potential benefits of the tele-exercise intervention for people with SCI and build upon adaptive intervention design and its delivery strategies that aim to increase adoption and sustainable exercise behavior. This pilot trial will inform future SMART-designed studies and provide new and innovative strategies for investigating intervention effects on physical activity behavior in the SCI population.

**Trial Registration:**

ClinicalTrials.gov NCT04726891; https://classic.clinicaltrials.gov/ct2/show/NCT04726891

**International Registered Report Identifier (IRRID):**

DERR1-10.2196/47665

## Introduction

Approximately 302,000 individuals in the United States are living with spinal cord injury (SCI) [1]. Substantial evidence supports the benefits of exercise training for improving health and functional outcomes and managing the risk of chronic disease and secondary conditions related to the SCI (eg, cardiometabolic disease, obesity, and depression) [2-8]. Despite the benefits, people with SCI engage in considerably lower levels of exercise and physical activity participation compared with the general population of adults and individuals living with other health conditions [4,9,10]. This may have resulted from a multilevel of barriers that people with SCI experience with exercise and physical activity participation in the community (eg, a lack of accessible facilities or options, knowledgeable instructors, transportation, or social support) [9].

Furthermore, people with SCI, who initiated engaging in an exercise behavior, often have varying rates of success in standardized exercise interventions, which have been designed using a traditional “one-size-fits-all” approach (ie, exercise group vs control) [11,12]. Previous studies have often demonstrated low levels of adherence to exercise programs, high dropouts, and a large portion of the sample not continuing exercise behavior throughout the follow-up [13-15]. In addition, home-based exercise programs are a desirable approach for overcoming barriers and facilitating full participation that could be of great assistance to people with SCI. Tele-exercise programs are potentially more cost-efficient and convenient (ie, do not require transportation or large travel times) than programs offered in the community, making it easier to reach larger groups of people with SCI [16]. Collectively, these findings suggest that the design of future home-based exercise training studies should be more targeted and tailored interventions for people with SCI.

Adaptive interventions provide a flexible treatment regimen based on the participant’s evolving status and specific needs, previously used in healthy behavior promotion research (eg, smoking cessation and weight loss) [17-20]. Sequential Multiple Assignment Randomized Trial (SMART) is an experimental design that enables investigators to answer whether, when, and how to alter treatment intensity and type to build an evidence-based adaptive intervention [21]. The use of the SMART design has the potential to optimize the design and delivery strategies of an exercise promotion intervention for maximizing adherence to the program in people with SCI; yet we are unaware of exercise interventions applied and tested this design for people with SCI.

We further note the importance of embedding behavioral approaches to increase physical activity in people with SCI. Based on prior research [22], the study design and delivery are grounded in social cognitive theory (SCT) [23,24], which has been used successfully to improve many health behaviors, such as diet and exercise adherence, in individuals with SCI. The main concept of SCT is the interplay between personal, environmental, and behavioral factors [25]. Outcome expectations [26-29], self-efficacy [28,30-32], social support [26,28,30,31], and self-regulation [26,31,33] are key constructs of SCT that have been associated with changes in various health behaviors in past studies, including several studies involving a broader group of people with mobility disability [27,30,33,34].

We propose a pilot, 2-phase SMART examining the feasibility of a 12-week tele-exercise intervention for improving adherence to the program and physical activity behavior in 30 adults with SCI, named the Sequential Multiple Assignment Randomized Trial for Home-based Exercise And Lifestyle Tele-Health (SMART-HEALTH). The applied exercise intervention is a novel movement-to-music (M2M) video program that incorporates enjoyable movement routines accompanied by music to improve cardiovascular capacity, muscular strength and endurance, balance, and range of motion. Evidence supports the efficacy of M2M in enhancing functional mobility (the timed up and go and 6-minute walk test) among adults with multiple sclerosis [35]. Also, 1 ongoing tele-exercise trial is testing the effectiveness of the M2M video program that includes >400 adults with physical disabilities (NCT03024320) [36]. The modified and scaled-up M2M program was delivered at a state-of-the-art exercise facility for people with disabilities (Lakeshore Foundation). This program integrates the principles of SCT through weekly newsletters that contained educational information aligned with the key constructs of SCT (self-efficacy, outcome expectation, knowledge, self-regulatory strategies, facilitators, or barriers) for promoting and maintaining behavior change.

The primary aim of this study is to assess the feasibility of the 12-week tele-exercise intervention with the SMART design application. The assessment of the feasibility focuses on recruitment or enrollment, adherence, and retention rates, resources and management issues, timing to identify nonresponders, and adverse events (AEs). The secondary aim is to qualitatively assess the acceptability of the SMART-HEALTH intervention. Acceptability will be assessed qualitatively via thematic analysis of semistructured exit interviews conducted at 3 months from baseline, with participants who complete the pilot study. The tertiary aim is to estimate average intervention effects and variability on the scientific outcomes (eg, video watch minutes, self-reported vs objectively measured physical activity) to determine effect sizes and potential for a larger trial. The information yielded by such a feasibility study will be critical for designing larger-scale projects that can establish the actual efficacy and effectiveness of the future SMART-HEALTH study.

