### Analysis

#### Overview

All data will be exported and analyzed using SPSS (version 22.0; IBM). Data will be initially examined for variations, outliers, errors, and patterns of missing values. Missing data will be inputted using multiple imputation techniques where necessary based on the assumption that the missingness mechanism is at random. All statistical analyses will be conducted in an intent-to-treat manner at the individual level.

#### Aim 1

The primary outcomes of this pilot study will include enrollment rate, retention rate, and completion rate of surveys and physiological measures. Process, resource, and management feasibility will initially be examined via percentage, frequency analysis, and descriptive statistics.

#### Aim 2

A qualitative study of participants’ experiences, perceptions, and suggestions regarding the SMART-HEALTH program will be completed at week 12. This study will refine the study components and implementation processes for a future trial. In brief, participants who complete the SMART-HEALTH program will take part in single, one-on-one semistructured interviews with questions focusing on what worked and did not work. Interviews will be audio-recorded, transcribed, and analyzed using thematic analysis using a qualitative descriptive design [43].

#### Aim 3

The study will estimate recruitment and retention rates, as well as estimate outcomes and variability of efficacy outcomes for a larger clinical trial (aim 3), which will measure rates of physical activity, psychosocial variables (eg, depression), and physiological variables (eg, lung function). Additional fidelity measures will include adherence to exercise intervention (minutes of sessions viewed), number of coaching sessions completed, and intervention safety (number of AEs).

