### Power

We will aim to enroll at least 40 people with SCI, considering 25% of the attrition rate based on the preliminary data obtained in the exercise intervention study with the M2M program [44]. The sample size of 30 participants aligns with the statistical recommendations for pilot trials to determine precise estimates, and the expectation that at least 5 participants will move each rerandomization group aligns with the statistical recommendations for the pilot SMART trial to determine precise estimates [45,46].

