### Strength and Limitations

The trial uses an innovative study design to address adherence to exercise interventions among people with SCI. It addresses a growing need among physicians treating patients with mobility disabilities to have easily accessible eHealth home-based exercise videos that can be tailored to the functional level of their patients. This is a pilot trial to assess the feasibility of using a SMART design and is not powered for effectiveness.

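### The tertiary aim uses effects estimated in about 30 people to determine effect sizes and a larger trial's potential, which estimates this imprecise cannot do

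*Protocol article*

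**What the plan says.** The Introduction gives three aims. Feasibility is primary and acceptability is secondary. The tertiary aim is to "estimate average intervention effects and variability on the scientific outcomes", and the stated purpose is "to determine effect sizes and potential for a larger trial". The Aim 3 paragraph of the Analysis section repeats the intention, together with recruitment and retention rates: "estimate outcomes and variability of efficacy outcomes for a larger clinical trial".

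The group sizes come from two places. Study Design randomises 30 people 1:1 to two first-stage groups and rerandomises nonresponders 1:1 to M2M Live or IBC. The Power section expects that "at least 5 participants will move each rerandomization group". It also says "We will aim to enroll at least 40 people with SCI", allowing for 25% attrition.

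Three statements describe what the trial can show:

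- Power: "The sample size of 30 participants aligns with the statistical recommendations for pilot trials to determine precise estimates".
- Strength and Limitations: the pilot "is not powered for effectiveness".
- Conclusions (Discussion): the trial can determine the actual efficacy of home-based exercise.

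**The concern.** The tertiary aim states a use of the data. The estimated effects are meant to settle two things: how large the effects are, and whether a larger trial has potential. Both need estimates precise enough to tell a worthwhile difference from none. At these group sizes chance alone produces differences as large as any that such a trial would plausibly target.

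Two harms could follow. An effect that looks large by luck gives an underpowered next trial if that trial is sized on it. An effect that looks small by luck counts against a strategy that works. The Introduction calls the information from this pilot critical for designing larger projects, so the error would pass to the next study.

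**Working it through.** **Inputs.** Analysable N is 30 and enrolment at least 40 (Power). Allocation is 1:1 at both stages (Study Design). At least 5 are expected per rerandomisation group (Power). No SD, alpha or target difference is stated, so I work in SD units with a two-sided 5% level and assume normal outcomes with equal variances.

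**The plan's own figure.** 30 / (1 − 0.25) = 40. The enrolment target reproduces, and this point does not concern it.

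**Group sizes.**
- First stage: 30 / 2 = 15 per group. If all 40 enrolled were analysed, 20 per group.
- Second stage within a first-stage group: 5 v 5 at the planned minimum.
- Second stage pooled over both first-stage groups: 10 v 10 at that minimum. Because 5 is a floor, the real numbers could be larger.

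**Precision.** With n per group, the standard error of a standardised difference is about √(2/n) near no effect. The half-width is t(0.975, 2n − 2) × √(2/n).

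| Comparison | √(2/n) | t | 95% half-width |
|---|---|---|---|
| 20 v 20 | 0.316 | 2.024 | 0.64 SD |
| 15 v 15 | 0.365 | 2.048 | 0.75 SD |
| 10 v 10 | 0.447 | 2.101 | 0.94 SD |
| 5 v 5 | 0.632 | 2.306 | 1.46 SD |

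An observed 0.5 SD at 15 v 15 thus has an interval of about −0.25 to 1.25 SD, which covers no effect and a very large one.

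**Chance findings on one contrast (illustration).** The document gives no cut-off, so I assume 0.5 SD in either direction. With no true difference, 0.5 / 0.365 = 1.37 on 28 degrees of freedom gives P = 0.18 at 15 v 15. The same sum gives 0.28 at 10 v 10 and 0.45 at 5 v 5.

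**Missed effects (illustration).** If the true difference is 0.5 SD, the observed one falls below 0.2 SD in about 20% of trials at 15 v 15 and 31% at 5 v 5.

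**Sizing the next trial (illustration).** For 80% power on an observed 0.8 SD, 2 × (1.96 + 0.84)² / 0.8² = 24.5 per arm, or 26 per arm by the t-test. If the true difference is 0.5 SD, the noncentrality is 0.5 × √(26/2) = 1.80 and the power is about 42%.

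**Statements side by side.** Strength and Limitations disclaims power for effectiveness. The Power section claims precise estimates from 30 participants, and the table contradicts that for between-group effects. The Discussion's Conclusions credit the trial with determining actual efficacy, whereas the Introduction leaves that to larger projects.

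**The case against.** The strongest reply is that this is a pilot with feasibility as its primary aim, which says openly that it is not powered for effectiveness. Its Aim 3 analysis is estimation only and already carries forward recruitment, retention and outcome variability. Nothing says that the next trial will be sized on the observed effect. A lead outcome, intervals and progression criteria may well sit in the full protocol or SAP. All of that stands, so I do not treat their absence as a fault, and the 42% figure is an illustration. What remains is the stated purpose of the tertiary aim, which goes beyond estimation.

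A reader might infer something stronger: that the basis for proceeding would be met most of the time even if no strategy differed from another. The documents do not support this, because they contain no rule whose pass rate could be computed. The answer depends on what one assumes. Counting 0.5 SD or more in either direction on any of 15 outcomes gives 76 to 91% at 15 v 15 (pairwise correlation 0.6 and 0.3). Any of 3 outcomes gives about 43% (correlation 0.3), and one contrast on one outcome 18%.

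The contrast is also open: average effects could mean change from baseline. With 30 people, a mean change has a half-width of about 2.045 / √30 = 0.37 SD of change. That is tighter, but it has no comparator and says nothing about which strategy is better.

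**Conclusion.** The point holds as a matter of stated use. Effects estimated in about 30 people cannot determine effect sizes or a larger trial's potential when the 95% half-width is about 0.75 SD at 15 v 15, 0.94 SD at 10 v 10 and 1.46 SD at 5 v 5. Analysing all 40 enrolled improves the first-stage figure only to 0.64 SD. These figures rest on normal outcomes, equal variances and the planned group sizes; they need no cut-off, outcome count or correlation.

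The protocol also describes its own reach inconsistently: Power and the Discussion's Conclusions claim more than Strength and Limitations allows.

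No claim is made about how often a go-forward decision would be wrong. Nor can the 25% attrition allowance be turned into a 75% retention benchmark for progression: the Power section uses it only to set enrolment. The trial's conduct and primary aim are unaffected. What changes is what the pilot may conclude and how the next trial is sized.

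**What to change.** Reword the tertiary aim in the Introduction and the Aim 3 paragraph of the Analysis section so that:

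1. potential for a larger trial is judged on the primary feasibility metrics;
2. Aim 3 carries forward outcome SDs and the nonresponse and retention rates, each with a confidence interval;
3. between-strategy differences are reported with confidence intervals, labelled descriptive, and not used to size the next trial;
4. the next trial's target difference is taken from a minimal important difference.

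Then bring two statements into line with Strength and Limitations: in Power, drop or qualify the claim of precise estimates; in the Discussion's Conclusions, remove the claim about actual efficacy.

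The cost is wording only, with no extra data or participants. The downside is that the sponsor can no longer cite pilot effect sizes as support for the larger trial.

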## Methods

### Study Design

This pilot study applied a 2-phase SMART design. Thirty adults with SCI will be randomized with equal probability into 1 of 2 asynchronous, M2M exercise programs (using prerecorded videos) at the first phase of the intervention. The exercise minutes of the pre-recorded videos are set to progressively increase from 30 to 150 minutes per week throughout the 12 weeks. The response assessment will be administered at weeks 3 (group 1) and 6 (group 2) based on the predetermined adherence criteria to the intervention (average of 95% video watch minutes, ranging from 29 minutes to 143 minutes). Participants who meet or exceed the criteria will be considered as responders and continue the asynchronous program for the entire intervention period, whereas those who did not meet the criteria (nonresponders) will be rerandomized with equal probability into either synchronous, instructor-led M2M exercise program (ie, switch to M2M Live group) or behavioral coaching with asynchronous M2M exercise program (ie, augment with individual behavioral coaching; IBC). The study flow diagram includes the details of the interventions offered in each arm (Figure 1).

**Figure 1 figure1:**
[figure not shown]
Sequential Multiple Assignment Randomized Trial for Home-based Exercise and Lifestyle Tele-Health (SMART-HEALTH) study design for people with spinal cord injury. IBC: individualized behavioral coaching; M2M: movement-to-music intervention; N: sample; R: randomize.

### Ethics Approval

Ethics approval was obtained from the institutional review board (IRB) of the University of Alabama at Birmingham on March 10, 2021 (IRB-300006746), and registered at ClinicalTrials.gov (NCT04726891). Informed consent will be obtained from all participants prior to the research activities. For privacy and confidentiality protection, all data will be collected and stored on a secure, web-based database application, referred to as Research Electronic Data Capture (REDCap; Vanderbilt University). Participants will receive up to US $160 of monetary incentives using direct deposit in a reloadable debit card (ie, ClinCard). This includes US $25 for baseline assessments, US $60 for weekly post workout surveys (US $5 for each survey×12 surveys), US $50 for post intervention assessments, and US $25 for an exit interview at the end of the 12-week intervention.

### Recruitment and Enrollment

We reviewed our database and identified 1016 persons who fit our inclusion criteria (disability status and expressed interest to participate in future research). Additionally, we identified 347 people with spinal cord dysfunction through an external database. We sent out invitation emails to all potential participants across the United States.

We advertised the study information through social media channels and the Lakeshore Foundation. The Lakeshore Foundation has the ability to distribute an electronic newsletter for people with SCI and other disabilities, social media channels, community events, and through the National Center on Health, Physical Activity and Disability (a center funded by the US Centers for Disease Control and Prevention).

Interested individuals can contact the study staff via phone, email, or online application linked with REDCap. A digital form of informed consent is given to eligible participants to review the study details, signed, and submitted. A project coordinator, who is responsible for participant communications and process management, follow-ups with the prospective participant via phone call, verbally reviews the consent form, answers any study-related questions and concerns, and guides the following study procedures.

### Randomization Allocations and Other Trial Considerations

Participants are potentially randomized up to twice throughout the 12-week intervention period. A study statistician generated 3 randomization sequences a priori using a computer-generated random schedule (SAS version 9.4; SAS Institute) with a 1:1 allocation ratio and a permuted block approach. The sequences were stored into a randomization module in the REDCap and external program, which allows project staff to unfold the randomization schedule when needed (after completing baseline assessment and after a 3-week or 6-week check-in call). One sequence was used to perform the first randomization of 30 participants into one of the asynchronous M2M exercise groups (group 1 vs group 2), whereas other 2 sequences were used to perform the second randomization of participants who need a transition from asynchronous M2M exercise to M2M Live or IBC based on the adherence rate to the intervention. Response assessment (ie, adherence rate to the program) will be administered at week 3 and week 6, respectively, for the intervention groups 1 and 2. Participants identified as responders who watched the video more than 95% (accounting for 5% error rate) will continue with the first treatment regime. Participants will be considered nonresponders if they adhere to the exercise program less than 95% using video watch minutes. This is based on observation with a few weight loss studies that suggested sessions 3 and 7 as potential time points for intervening with participants to assess needs and difficulties and make necessary changes to maximize the treatment response [39-42].

The outcome assessor will be blinded to group allocation (single-blinded trial design). Due to the nature of the intervention, it is not plausible to blind participants and study staff who enroll participants and monitor the intervention delivery. However, study investigators and staff who are involved in data analyses and reporting will be blinded to group assignments throughout the study period.

Access to the REDCap database will be given to the study personnel only, including the biostatistician and data entry or management personnel. Data that are analyzed will be exported in a deidentified format. The identities of participants will not be revealed in the presentation or publication of any result from this project.

